
Appendix I

Visual analogue scale (VAS) charts (Alghadir et al., 2018; Boonstra et al., 2008).

[figure not shown]

[figure not shown]

無痛

劇痛

Appendix II

Chinese version KOOS questionnaire (Roos et al., 2003; Cheung, Ngai and Ho., 2016)

[figure not shown]

[figure not shown]

[figure not shown]

Appendix III

Kellgren and Lawrence system (Petersson et al., 1997)

Grade 0: no radiographic features of OA are present

Grade I: doubtful joint space narrowing (JSN) and possible osteophytic lipping

Grade II: definite osteophytes and possible JSN on anteroposterior weight-bearing radiograph

Grade III: multiple osteophytes, definite JSN, sclerosis, possible bony deformity

Grade IV: large osteophytes, marked JSN, severe sclerosis and definite bony deformity

Appendix IV

Data collection form

| Case identity | Date of assessment | Age | Gender | | | BMI | | Unilateral/Bilateral knee pain | | Duration of knee pain | Any injury |
| --- | --- | --- | --- | --- | --- | --- | --- | --- | --- | --- | --- |
|  |  |  | M / F | | | Height: M  Weight: Kg | | R ______  L ______  Both ___ | | ___months | (Y / N) |
| Severity of pain (VAS) | KOOS-Pain score | KOOS-  symptoms  score | KOOS_ADL score | | | Remarks (any any discomfort or side effects): | | | | | |
| _____ mm | ______/36 | ______/28 | ______/68 | | |
|  |  |  |  | | |
| Number of needle used  ( ) | Areas applied dry needling or acupuncture  Oblique/perpendicular insertion: / | | | | |  | Nausea/faint/ hypodermal bleeding others:  _______________________________ | | | | |
| Compliance of exercises: |  | | | | XR: KL scale: Grade 0 / I / II /III /IV | | | | | | |
| Tablets of medication |  | | | Number of tender spots: | | | | | Depth of insertion (mm): | | |
| Ultrasound findings | Patient code: ___________  Real US-dry needling: Y/N  Findings: __Power Doppler of blood flow increased/decreased (neovascularity +/-)  Mucoid degeneration/increased thickness/hypoechogenecicity/hyperechogenecity  __________________________________________________________________________________  __________________________________________________________________________________  __________________________________________________________________________________ | | | | | | | | | | |
| Location of dry needling | [figure not shown]  L medial  R medial | | | | | | | | | | |

Key: Q= quadriceps strength, H= hamstrings strength, ROM=range of motion, R= right and L= left, M=male, F=female, Y= yes and N= no, MMT: manual muscle testing

Scales: mm= minimeter, N=newton, 0 is degree of angle

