**Methodology:**

1. Study Design

A randomized, double-blinded, controlled, parallel group, repeated-measures design will be used. Ethical approval will be obtained from The Hong Kong Polytechnic University and Caritas Institute of Higher Education. The trial will be conducted in accordance with the Declaration of Helsinki.

1. Study subjects

Based on the effect sizes from previous relevant studies, the sample size has been calculated and 90 patients with KOA will be recruited from the general public with the physiotherapy referral from a doctor with the diagnosis of KOA and screened by knee X-ray with the Kellgren and Lawrence (KL) scale (Petersoon et al., 1997). Their age, gender, body mass index (BMI), unilateral or bilateral knees involved, duration of knee pain and any history of knee injury will be recorded as baseline information. The current study targets in mild to moderate degenerative KOA with XR showing with the KL scale (Petersoon et al., 1997) grade I and grade III (which is most beneficial to conservative treatment) (Appendix III). KL scale was proposed in 1957 and accepted by the WHO in 1961, it has been widely used in grading the severity of KOA (Samuel & Kanimozhi, 2019). All the classification of XR with the KL scale in this study will be done by a physiotherapist who has more than 10 years experience in musculoskeletal conditions and training in interpretation of knee XR with the classification of KL scale. All the subjects meet the inclusion criteria will be allocated by computer randomized program that will be created by a statistician who is not otherwise involved in the trial and does not participate in analysis or interpretation of the results. The allocation sequence will be concealed from the principal investigator enrolling and assessing participants as each participant’s allocation which will be contained in sequentially numbered sealed and stapled opaque envelopes. All the eligible subjects will be allocated into G1, G2, and G3. Each group will recruit 30 subjects. The assessor will be blinded to the patient’s treatment group assignment at all time and will carry all the baseline, 4-week and 8-week evaluations.

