Inclusion criteria were based on previous relevant studies (Itoh et al., 2008; Sánchez-Romero et al., 2018). Inclusion criteria were as follows: 1) >50 to 80 years old, 2) referred with a diagnosis of KOA (i.e., primary KOA fulfilling the American College of Rheumatology criteria developed by Altman et al. (1986) (at least three out of six) for clinical and radiographical diagnostic KOA 3) presenting with anterior and/or medial knee pain with 2-3 local tender spots, 4) crepitus, 5) functional limitations caused by KOA over a period of at least six months, 6) stiffness <30 minutes, 7) KL scale (Petersson et al.,1997) of grade I to grade III; and 8) able to read Chinese and communicate in Cantonese based on literacy.

Exclusion criteria, made with reference to previous studies (Itoh et al., 2008; Sánchez-Romero et al., 2018), were: 1) having knee pain less than 6 months; 2) having other musculoskeletal diseases associated with knee pain (e.g., referred pain from the low back or posterior or lateral knee pain or co-existing pain over the other limb); 2) suffering from acute inflammation, diffuse tenderness upon palpation test, bone marrow lesion, severe joint deformity with X-rays revealing a grade IV in the KL scale (Petersson et al., 1997), coagulation disorders, metabolic, or neuropathic arthropathies, immunosuppressed or systematic disease; 3) having severe concomitant illness that might affect the clinical outcomes of this study, 4) contraindications to DN including pregnancy, malignancy, fear of DN; 5) having recent treatment involving acupuncture or DN therapy or non-pharmacological intervention (e.g., physiotherapy) within a month prior to the start of the study; 6) inability to answer questionnaires and non-responsiveness towards the assessor; 7) having a wound or pressure sore or skin problems or skin allergy, including an allergy to iodine; and 8) having a history of injecting steroids.

Participants will be provided with written information sheets and verbal explanations. Written consent will be signed. They can withdraw from the study at any time. All the adverse effects, if any, will be recorded and reported in this study. The group allocation and data will be concealed in a password-protected computer file only accessible by the principal investigator.

Table 1: Participants flow chart:

Recruit from advertisements on social media and assessed by orthopedic surgeon for eligibility of KOA

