
For the G2, the subject will also be positioned in a supine position same as G1. Then the physiotherapist (same therapist as in G1) will wash hand and take sterile gloves, and then do the disinfection to the skin in the target DN sites. DN will be applied to the most painful sites. To blind the patients with a placebo US-guide, the physiotherapist will do the procedure of scanning as G1 but with US monitor’s screen, out-of-view from the G2 patient’s vantage point, was turned off to blind the subjects. Then the needling will be manipulated every 5 minutes and the whole treatment time will be 15 minutes. The whole procedure similar as mentioned in G1, but there is no US scanning. After the treatment finished, sterile gauze will be applied and pressed on the side of DN. The physiotherapist will state with the subject for the whole procedure to ensure safety.

For G3, the subjects received only standardized exercise therapy and educational materials related to the care of their knees. The exercise therapy was conducted under the supervision of a registered physiotherapist weekly for 4 sessions. The exercises focused on improving knee mobility, soft tissue flexibility, muscle strength, balance and proprioception. The participants were instructed to continue the exercises at home three times per week for another four weeks.

All the outcomes will be assessed by an independent research assistant.

Details of outcomes assessment

1. The Visual Analogue Scale (VAS) is commonly used in measuring musculoskeletal pain with a 100mm horizontal line anchored with labels on top of it (Appendix 1). The reliability of the VAS for disability is moderate to good (Boonstra et al., 2008) and VAS is the most reliable tool in assessing pain as compared with numerical rating scale (NRS) and verbal rating scale (VRS), with the smallest errors in the measurement of osteoarthritis knee pain (Alghadir et al., 2018). The minimum clinically important difference (MCID) was 19.9 mm (Katz et al., 2015; Tubach et al., 2005).

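### Assessor blinding and allocation concealment are contradicted and left unprotected by the Appendix IV form and the rule on who holds the allocation file

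*Protocol*

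**What the plan says.** **Blinding.** The Study subjects text under Methodology states: "The assessor will be blinded to the patient’s treatment group assignment at all time". The same person is to do the baseline, 4-week and 8-week evaluations. The method of data analysis adds that the analyses are run blind to group by an independent research assistant.

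**Concealment.** An otherwise uninvolved statistician creates the sequence, and each allocation sits in a numbered, sealed, opaque envelope. On who is kept from it: "The allocation sequence will be concealed from the principal investigator enrolling and assessing participants".

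**Custody of allocations.** After the exclusion criteria: "The group allocation and data will be concealed in a password-protected computer file only accessible by the principal investigator".

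**Who assesses.** At the end of the description of the three arms: "All the outcomes will be assessed by an independent research assistant". Outcomes measures likewise gives exercise compliance at 4 and 8 weeks to an independent assessor.

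**The form.** Appendix IV has one date of assessment. It carries the VAS score, the KOOS scores, exercise compliance and medication, and also "Number of needle used", areas needled, depth of insertion, ultrasound findings, location of needling and "Real US-dry needling: Y/N".

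**The concern.** Both primary outcomes, VAS pain and KOOS, are reported by the participant. An assessor who knows the arm can still influence how such answers are prompted, clarified and recorded. The comparison of real with placebo ultrasound guidance is especially exposed, because the design goes to some trouble to make those two arms look alike. Bias that enters during data collection cannot be removed in the analysis.

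The second protection, concealment before assignment, matters at enrolment. If the person who decides on entry can look up earlier allocations, that person may gain information about later ones.

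The form layout, the custody of the file and the identity of the assessor are all fixed in this protocol, and they do not agree with one another. This is therefore not detail that could properly be left to a statistical analysis plan.

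**Working it through.** The plan gives no figure to reproduce, and no power or sample-size input bears on the point. The check is a comparison of the protocol's own statements.

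**1. What a completed form reveals.** The planned arms are G1 = 30, G2 = 30 and G3 = 30.

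| Item on Appendix IV | What it distinguishes |
|---|---|
| Needle number, areas, depth, location | Needled (G1 + G2 = 30 + 30 = 60) from not needled (G3 = 30) |
| Real ultrasound guidance, yes or no | G1 (30) from G2 (30) |
| Ultrasound findings | Probably G1 from G2, since the screen is off in G2 (my inference) |
| Tick-box for hypodermal bleeding | Suggests needling |

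The first two rows are enough. Yes means G1, no with needling entries means G2, and blank needling fields point to G3. That covers 60 + 30 = 90 participants. With two follow-up assessments each, up to 90 × 2 = 180 outcome records could be exposed. This is an upper bound that assumes the assessor sees every completed form.

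**2. Is the form only a therapist's record?** The text suggests not. It has a cell for exercise compliance, which Outcomes measures assigns to an independent assessor. It has a single assessment date. The participant flow chart sets the first follow-up immediately after the last treatment session, so treatment and outcome entries can fall close together. No section provides a separate outcome sheet, masking of the treatment fields or an order of completion.

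**3. Who is the assessor?** There are two readings.

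- *The principal investigator*, if assessing participants includes outcomes. This person alone can open the allocation file, which contradicts the promise of blinding.
- *The independent research assistant.* The file is then not the problem, but Appendix IV as printed would show this person the arm unless its parts are separated, and the protocol does not say that they are.

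Neither reading leaves the blinding protected by what is written.

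**4. Concealment.** The envelopes can still hide the next assignment. The file holds group allocation, but the protocol does not say whether that means past assignments only or the whole sequence. If it is past assignments only, the gain to the enrolling person depends on how the sequence is restricted, which is not stated. If exactly 30 per arm were enforced, the 90th assignment would follow with certainty from the first 89, and some information would build up as arms filled. How far this reaches back cannot be worked out from the text.

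**The case against.** The strongest reply has four parts.

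- **The outcomes have their own instruments.** The VAS chart is Appendix I and the KOOS questionnaire Appendix II. Appendix IV holds only score cells, so it may be a summary sheet filled in later. Its ultrasound block has its own patient-code line, which may mean that it is completed separately. No section says who fills which cell. This stands: a reader might infer that the assessor necessarily sees the arm, and the documents do not establish that.
- **Assessing may mean eligibility.** The phrase about the principal investigator sits in the sentence on concealment before allocation, and two other places point to an independent assessor. This also stands. That the principal investigator measures the outcomes is one reading, not a stated fact.
- **Holding a file is not breaking concealment.** Envelopes prepared from an independent statistician's sequence can coexist with a protected record of past allocations. A reader might infer that the enrolling person can see the next assignment, but the protocol does not say that the file contains it.
- **Some unblinding is beyond any form.** G3 participants know they were not needled and may say so. Most needling fields do not separate G1 from G2; the yes/no item does.

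These points limit the claim without removing it. The blinding promise is explicit, the printed form and the custody rule run against it, and nothing in the protocol reconciles them.

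**Conclusion.** The point holds in this form: assessor blinding and allocation concealment are contradicted, and not protected, by the protocol as written. The conclusion that they cannot hold would go too far, because the protocol does not say who completes which part of Appendix IV, what the allocation file contains, or whether the investigator's assessing extends to outcomes.

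The possible reach is all 90 participants at both follow-ups, on the assumption that the assessor handles complete forms. The size of any bias in VAS or KOOS cannot be computed from the document. The matter is still more than a missing detail: it affects both primary outcomes in a trial described as double-blind, analysis cannot repair it afterwards, and the correction is nearly free.

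**What to change.** 1. **Split Appendix IV.** An outcome sheet for the blinded assessor carries VAS, KOOS, exercise compliance, medication and general adverse events. A treatment sheet for the therapist carries needle number, sites, depth, ultrasound findings, real or placebo guidance, and needle-specific events such as hypodermal bleeding, which would otherwise hint at the arm.
2. **File the two sheets separately.** State that the treatment sheet is withheld from the assessor and from the blinded analyst until database lock.
3. **Move custody of the allocation file** to someone already on the trial who neither enrols nor assesses. The independent statistician is one option; the description of that person as not otherwise involved would then need amending. State what the file contains.
4. **Name one outcome assessor.** Reword the concealment sentence under Study subjects so that the independent research assistant is the only person who assesses outcomes, and any assessing by the principal investigator is limited to eligibility.

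The cost is a form re-layout and a few sentences, with no added staff, and two sheets per participant to be linked by patient code. The change will not stop G3 participants from disclosing their arm to the assessor.

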Appendix V

US scanning procedure (Jacobson 2018).

Part 1. Anterior patella-femoral compartment:

Patello-femoral compartment (Figure 1 of Appendix VI) (Sengupta et al. 2006): the structures will be evaluated from anterior part of the knee joint including the quadriceps muscles, quadriceps tendon, the patella, the patella tendon, the patella retinaculum, the suprapatellar recess, the medial and lateral recesses (Table 1 of Appendix VI).

1. Examination will be begun in the sagittal plane 2 cm proximal to the base of patella (Figures 2A and 2B of Appendix VI). Slight flexion of the knee in 300 with a roll of towel behind the knee that is often helpful because this position straightens and tenses the extensor mechanism to reduce tendon anisotropy.
2. The quadriceps tendon is then evaluated in short axis (Figures 3A and 3B of Appendix VI)
3. Then the US probe is turned back to sagittal and milks the suprapatellar recess by shifting the joint fluid from other distal part of the knee joint to see any abnormal joint effusion.
4. The transducer is then moved inferiorly below the patella in the sagittal plane to exam the patellar tendon whether it is in a hyperechoic, fibrillar, and uniform pattern (Figures 4A and 4B of Appendix VI).
5. The Hoffa infrapatellar fat pad appears slightly hyperechoic and underneath to the patellar tendon. The region around the distal patellar tendon is also evaluated for superficial and deep infrapatellar bursal fluid; minimal fluid is considered to be normal pattern (Figures 5A and 5B of Appendix VI).
6. The transducer is then moved to both the medial and lateral margins of the patella in the transverse plane to see the thin hyperechoic patellar retinaculum. With distention of the medial and lateral recesses by milk them with joint fluid from the surrounding structure that are continuous examination with the suprapatellar recess, which is more apparent when the knee is completely extended. In addition, the medial patellofemoral ligament (MPFL) and patello-tibial ligament (MPTL) will also be visualized (Figures 6A and 6B of Appendix VI). The medial patellofemoral ligament is located from the medial femoral epicondyle and adductor tubercle running obliquely to insert to the upper 2/3 medial border of the patella (Figures 6A and 6B of Appendix VI). The patella-tibial ligament is origin from medial tibial tubercle and run slightly obliquely to insert to the medial lower1/3 of the medial patella (Figures 7A and 7B of Appendix VI).
7. Finally, with the knee in flexion, the hypoechoic hyaline cartilage that covers the trochlea of the anterior femur can be appreciated in the transverse plane superior to the patella. A uniform thin layer of hypoechoic hyaline cartilage covering the anterior and central aspects of the femoral condyles can be seen in the parasagittal plane in non-pathological subjects (Figures 8A and 8B of Appendix VI).

Part 2: medial tibio-femoral compartment (Sengupta et al. 2006):

1. For medial knee evaluation, the patient remains supine and slightly rotates the hip externally to gain access to the medial knee structures. The structures of interest include the medial collateral ligament, the anterior horn and medial part of the body of the medial meniscus, and the pes anserinus. To begin, the transducer is placed in the coronal plane along the medial joint line, which is identified by the bone contours of the femoral condyle and the proximal tibia (Figures 9A and 9B of Appendix VI). The medial collateral ligament appears as a thick hyperechoic and fibrillar superficial layer that is easily identified in long axis; it extends proximally from the medial femoral condyle, and distally to the slightly antetior proximal tibial metaphysis.
2. With turning of the transducer short axis to the medial collateral ligament, the anteroposterior extent of this structure can be appreciated (Figures 10A and 10B of Appendix VI).
3. Then the transducer will be turned back to the long axis to the tibial collateral ligament, thinner hyperechoic deep layers of the medial collateral ligament, also called the meniscofemoral and meniscotibial ligaments, are identified from the meniscus to the femur and tibia, respectively (Figure 9B of Appendix VI). The fibrocartilage meniscus is located as a triangular hyperechoic structure between the femur and the tibia. The transducer is then moved anteriorly from the coronal plane in the oblique-sagittal plane to examine the anterior horn of the medial meniscus.
4. The transducer is then moved distally below the joint line along the tibial collateral ligament and slightly anterior to its attachment on the tibia, around 4 cm below the joint line (Figures 11A and 11B of Appendix VI). Here, the pes anserinus can be seen as three hyperechoic tendons superficial to the tibial collateral ligament that converge onto the tibia and in a sequence of Sartorius, Gracilis and Semitendinosus tendons.

**Appendix VI**

Knee sonographic examination-checklist (Jacobson 2018).

| 1. Anterior and medial patellofemoral compartment |
| --- |
| 1. The most common anatomical locations of pain in OAK patients   [figure not shown]  **Appendix VI Figure 1.** The most common anatomical locations of pain in OAK patients (Sengupta et al. 2006). |
| **Appendix VI Figure 2A**. shows the position of anterior knee US scanning for the Sagittal view and 2B shows the quadriceps tendon (black arrowheads), quadriceps fat pad (Q), prefemoral fat pad (PF), and collapsed joint recess (white arrow), F=femur and P=patella (Jacobson 2018).  [figure not shown] |
| **Appendix VI Figure 3A and 3B.** Short axis of quadriceps femoris (Figure 3A) and the quadriceps tendon (arrowheads) (Figure 3A).  [figure not shown] |
| **Appendix VI Figure 4A and 4B.** US scanning to patella tendon in sagittal view (Figure 4A) and the patella tendon (arrowheads) and Hoffa fat pad (H). P=patella and T=tibia in (Figure 4B).  [figure not shown] |
| **Appendix VI Figure 5A.** US scanning to patella tendon in transverse view (Figure 5A) and the patella tendon (arrowheads) and Hoffa fat pad (H) in Figure 5B.  [figure not shown] |
| **Appendix VI Figure 6A**. US scanning to patellofemoral tendon in longitudinal view (Figure 6A). The medial knee joint recess (white arrow) and the arrowheads show the patellofemoral ligament (Figure 6B) and position of patellofemoral ligament in medial knee (Figure 6C). F=femoral condyle, P=patella.  [figure not shown]  **Appendix VI Figure 6C.** The location of the medial patellotibial ligament (MPTL), medial patellofemoral ligament (MPFL) and it runs obliquely and transverse origin from the femoral epicondyle and adductor tubercle. Around the vastus medialis oblique muscle (VMO), the medial collateral ligament (MCL), and the adductor magnus tendon (AMT) are outlined with dotted lines (Jacobson 2018).  [figure not shown] |
| **Appendix VI Figure 7A**. US scanning to patellotibial tendon in longitudinal view (Figure 7A) and position of patellotibial ligament in medial knee (Figure 6C). The arrowheads show the patellotibial ligament (Figure 7B). T=tibial condyle, P=patella.  [figure not shown] |
| **Appendix VI Figure 8A.** Trochlear and femoral condyle cartilage. Figure 8A shows hypoechoic hyaline cartilage (arrowheads). LC=lateral femoral condyle, MC=medial femoral condyle, P=patella.  [figure not shown] |
| **Appendix VI Figure 9A.** Medial knee sonography evaluation in coronal plane (Figure 9A). Coronal imaging at the medial joint line is shown in (Figure 9B) the superficial (arrows) and deep (arrowheads) layers of the medial collateral ligament, and medial meniscus (white arrow). F=femur, T=tibia.  [figure not shown] |
| **Appendix VI Figure 10A**. Sonography examination of the medial collateral ligament in transverse plane (Figure 10A). Transverse imaging shows the medial collateral ligament (arrowheads). F=femur.  [figure not shown] |
| **Appendix VI Figure 11A.** Distal medial collateral ligament and pes anserinus. Coronal imaging distal to knee joint shows (Figure 11A), the superficial layer of the medial collateral ligament (arrowheads) and the tendons of the pes anserinus (arrows) (T=tibial metaphysis). Sonographic imaging in long axis shows the semitendinosus proximal to pes anserinus (arrowheads).  [figure not shown] |

